### Current status and baseline characteristics

The trial completed enrolment and randomization of 220 patients with kidney failure with or without residual urine output between October 2022 and January 2025 across nine sites in Austria. The baseline characteristics of the study population are presented in *Table 2*. Overall, the median age of the study population is 67 years (Q1–Q3: 57–75 years), 26% of participants are women, 42% have type 2 diabetes mellitus, 39 % have established coronary artery disease, and 28 % of patients have residual urine output ≤200 ml/day. Baseline echocardiography showed a mean LVMI of 138 g/m^2^ (standard deviation 37 g/m^2^) and a median LVEF of 59 % (Q1–Q3: 54%–65%) with 10% having an LVEF ≤40%; the median NT-proBNP concentration was 2911 pg/ml (Q1–Q3: 1181–7602 pg/ml).

**Table 2 xvag104-T2:** Baseline characteristics of the overall DAPA-HD trial population (N = 220)

	Overall
Age, years (median, IQR)	67 (57–75)
Female sex, *n* (%)	57 (25.9%)
BMI, kg/m^2^ (mean ± SD)	28.2 (5.1)
Type 2 diabetes, *n* (%)	92 (41.8%)
LVEF ≤40%, *n* (%)	19 (9.7%)
Atrial fibrillation, *n* (%)	27 (12.3%)
Coronary artery disease, *n* (%)	86 (39.1%)
Hypertension, *n* (%)	193 (87.7%)
Presumed primary cause of kidney failure	
Diabetes, *n* (%)	58 (26.4%)
Hypertension, *n* (%)	23 (10.5%)
Polycystic, *n* (%)	20 (9.1%)
Nephritis, *n* (%)	32 (14.5%)
Other/Unknown	87 (39.5%)
Residual urine volume ≤200 ml/day, *n* (%)	62 (28.2%)
Baseline medication:	
ACEi/ARB, *n* (%)	112 (50.1%)
Beta-blockers, *n* (%)	160 (72.7%)
Loop diuretics, *n* (%)	111 (50.5%)
Insulin, *n* (%)	42 (19.1%)
MRA, *n* (%)	12 (5.5%)
Baseline echocardiographic measurement:	
LV mass, g (mean ± SD)	266 (77.0)
LV mass index, g/m^2^ (mean ± SD)	138 (36.7)
LVEF, % (median, IQR)	59 (54–65)
NT-proBNP, pg/ml (median, IQR)	2911 (1181–7602)

Abbreviations: IQR, interquartile range; SD, standard deviation; BMI, body mass index; ACEi/ARB, angiotensin-converting enzyme inhibitor/angiotensin II receptor blocker; MRA, mineralocorticoid receptor antagonist; LV, left ventricular; NT-proBNP, N-terminal pro-B-type natriuretic peptide

## Discussion

The DAPA-HD trial is the first randomized controlled trial to evaluate the cardiovascular effects of SGLT2i in patients with kidney failure receiving maintenance haemodialysis.

Cardiovascular disease remains the predominant cause of death among haemodialysis patients, with adverse cardiac remodelling developing in response to pressure and volume overload as a major contributor to adverse events.^4,14,15^ Chronic kidney disease drives a complex interplay of pathophysiological processes, including activation of the renin-angiotensin-aldosterone and sympathetic nervous systems, oxidative stress, systemic inflammation, and profibrotic signaling.^16–19^ These mechanisms, together with vascular calcification and endothelial dysfunction that increase arterial stiffness and cardiac afterload,^20^ and along with sodium and fluid retention, ultimately lead to ventricular hypertrophy and fibrosis. For patients with kidney failure undergoing haemodialysis, traditional cardioprotective therapies, including statins, have shown limited efficacy, reflecting a shift in pathophysiology toward nonatherosclerotic mechanisms such as left ventricular hypertrophy, arrhythmias, vascular calcification, and sudden cardiac death.^21,22^ Thus, preventing or reversing maladaptive cardiac remodelling is a major unmet therapeutic need in this population.^23^

Heart failure assessment in dialysis patients, however, is challenging due to the dynamic nature of volume overload and the limitations of conventional NYHA or AHA/ACC classifications in this population. The Acute Dialysis Quality Initiative (ADQI) XI work group, therefore, proposed a functional classification that integrates echocardiographic evidence of structural or functional cardiac abnormalities (e.g. left ventricular mass) and dyspnoea assessment before and after renal replacement therapy.^24^ DAPA-HD was thus designed to assess change in left ventricular mass index as the primary endpoint, a validated surrogate of cardiovascular risk and a sensitive marker of reverse remodeling.^23,24^ Stratification by residual urine volume will provide additional exploratory mechanistic insights into whether potential cardiac effects of dapagliflozin depend on residual kidney function.

SGLT2i confer cardiovascular benefits independent of glucose lowering and across a wide range of kidney functions, down to an eGFR of 20 ml/min/1.73 m^2^.^7,25^ Their multifaceted effects involve modest reductions in blood pressure and plasma volume, natriuresis, improved tubular-glomerular feedback, increased erythropoiesis, ketone body-mediated energetic shifts, decreased sympathetic activity, and reduction in inflammation, oxidative stress, and fibrosis.^26–28^ However, many of these effects are presumed to depend on residual kidney function and active sodium-glucose cotransport, raising questions about whether SGLT2i retain efficacy in the absence of glomerular filtration. Evidence regarding SGLT2i use in dialysis populations is currently limited to observational analyses and small pilot studies, which suggest acceptable short-term safety but are insufficient to establish cardiovascular efficacy due to inherent confounding and limited sample size.^29^ By integrating comprehensive echocardiographic assessments, biomarkers, safety monitoring, and quality-of-life measures, DAPA-HD is designed to provide comprehensive mechanistic and safety insights into the effects of dapagliflozin in patients with kidney failure receiving maintenance haemodialysis. The trial tests a central biological hypothesis that SGLT2i may confer cardiovascular benefits even in patients with complete anuria, implying kidney-independent mechanisms, potentially mediated by systemic metabolic, haemodynamic, or neurohumoral modulation. Either outcome will advance our understanding of SGLT2i biology and inform their use across the CKD-to-dialysis transition, and complement the ongoing event-driven Renal Lifecycle trial (NCT05374291), which evaluates dapagliflozin on cardiorenal outcomes, including kidney failure, heart-failure hospitalization, and all-cause mortality in 1500 patients across a broad spectrum of patients with CKD, including patients with an eGFR ≤25 ml/min/1.73 m2, those receiving haemodialysis or peritoneal dialysis and kidney transplant recipients, while also incorporating imaging substudies to assess cardiac structure and function.^30^

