### Study objectives and endpoints

The primary endpoint of DAPA-HD is the change in left ventricular mass indexed to body surface area (LVMI), as measured by echocardiography after 6 months of treatment. Originally, the primary endpoint was defined as the change in LVMI measured by cardiac magnetic resonance imaging (cMRI). Shortly after study initiation and prior to unblinding, the primary imaging modality was changed to transthoracic echocardiography due to feasibility considerations and resource constraints inherent to an investigator-initiated trial. This protocol amendment was approved by the institutional ethics committee, and a revised sample size calculation was conducted accordingly.

Additional echocardiographic outcomes of interest include changes in left ventricular ejection fraction (LVEF), left atrial diameter, and strain analysis of the left atrium and the left and right ventricles. Additional assessments include changes in blood pressure, heart rate, metabolic parameters (including HbA1c, insulin, c-peptide, glucagon, β-hydroxybutyrate, GLP-1, cortisol, growth hormone, and pyruvate), cardiovascular biomarkers (hsTnT and NT-proBNP), and quality of life. All hospitalizations and deaths were recorded throughout the study period. Safety monitoring was conducted at each dialysis visit, with particular attention to signs of euglycemic ketoacidosis, genital infections, and electrolyte disturbances.

A key exploratory objective of the trial was to assess whether the cardiovascular effects of dapagliflozin are modified by residual urine volume. A prespecified subgroup analysis will compare treatment effects between patients with residual urine output >200 ml/24 hours versus ≤200 ml/24 h.

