### Statistical considerations

A sample size of 186 patients was calculated to provide 90% power to detect a 7 g/m^2^ difference in the primary endpoint at a two-sided alpha of 0.05, assuming a standard deviation of 15 g/m^2^. Accounting for an anticipated dropout rate of 20%, the target enrolment was set at 220 patients. The primary hypothesis will be tested using an analysis of covariance, adjusting for baseline LVMI. The primary analysis will use a complete-case approach, including all patients with available baseline and 6-month LVMI measurements. To assess the robustness of findings under alternative missing data assumptions, sensitivity analyses will be conducted using (i) multiple imputation assuming data are missing at random, with imputation models including baseline LVMI, treatment assignment, residual urine output stratum, age, sex, and diabetes status; and (ii) pattern-mixture models to evaluate potential bias under missing not at random scenarios, including differential dropout due to death or clinical deterioration. The extent and pattern of missing data will be reported descriptively by treatment group. In prespecified subgroup analyses, outcomes will be tested with interaction terms in the ANCOVA model to assess effect modification. Serious adverse events and study drug discontinuations will be summarized descriptively by treatment group.

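### The Discussion says the trial tests benefit in complete anuria, but the only contrast described is an exploratory, imprecise split at 200 ml/24 h of self-reported urine volume

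*Protocol article*

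**What the plan says.** The Discussion of the protocol article states: "The trial tests a central biological hypothesis that SGLT2i may confer cardiovascular benefits even in patients with complete anuria, implying kidney-independent mechanisms". It adds: "Either outcome will advance our understanding of SGLT2i biology".

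The design behind this is given earlier. Under Study objectives and endpoints: "A prespecified subgroup analysis will compare treatment effects between patients with residual urine output >200 ml/24 hours versus ≤200 ml/24 h". Treatment protocol and follow-up procedures says that the volume is the patient's own report at study entry. Statistical considerations says that effect modification will be assessed with interaction terms in the ANCOVA. Current status and baseline characteristics reports that "28 % of patients have residual urine output ≤200 ml/day", which Table 2 gives as 62 of 220. The article speaks of enrolling patients with or without residual urine output, but gives no count of patients who pass none.

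The sample size concerns the overall comparison only: "A sample size of 186 patients was calculated to provide 90% power to detect a 7 g/m^2^ difference in the primary endpoint". No power is stated for the interaction or for either stratum. Study objectives and endpoints labels the effect-modification question exploratory, and an earlier paragraph of the Discussion does the same.

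**The concern.** Two things separate the Discussion sentence from the design.

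The first is the population. Complete anuria means no urine, whereas the low stratum runs from zero to 200 ml/24 h by self-report. A patient passing 150 ml belongs to it and has some remaining kidney activity. The Background itself treats urine output as a pragmatic stand-in for kidney function. A benefit in this stratum would therefore be compatible with a kidney-dependent mechanism.

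The second is precision. The low stratum holds about 28% of the patients, in a trial sized for its main effect. If the interaction is too imprecise to tell a full effect from none, a non-significant result says little about whether benefit depends on residual kidney function.

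At stake is the mechanistic conclusion, including what is said about patients without urine output. The primary result is not at stake.

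**Working it through.** **Inputs from the article.** Difference 7 g/m², SD 15 g/m², two-sided alpha 0.05, 90% power, 186 evaluable, 20% dropout and 220 enrolled (Statistical considerations); 1:1 allocation (Treatment protocol and follow-up procedures); 62 patients at or below 200 ml and so 158 above (Table 2).

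**Assumptions.** SD 15 applies in both strata as the residual SD of the analysis; allocation is balanced within strata; dropout is the same in both strata.

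**The plan's own figure first.** Per arm, n = 2 × (1.96 + 1.2816)² × 15² / 7² = 96.5, so 97 per arm or 194 in total, against 186 stated. With 93 per arm the power is 88.9%. The stated 186 is not reproduced exactly but is close in power. That is a separate matter, and nothing below depends on it.

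**Formulas.** In a stratum of n patients allocated 1:1, the SE of the treatment effect is 15 × √(4/n). The SE of the interaction is 15 × √(4/n_low + 4/n_high). Power is Φ(difference/SE − 1.96). The difference detectable with 80% power is 2.80 × SE. The 95% half-width in the low stratum is 1.96 × 15 × √(4/n_low).

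**Two versions of no effect in the low stratum.**
- 7 g/m² in the high stratum and 0 in the low. The overall effect is then 7 × 158/220 = 5.0 g/m².
- Overall effect 7 g/m², all of it in the high stratum. The effect there is 7/(158/220) = 9.75 g/m².

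**Worked case, 20% dropout.** 220 × 0.8 = 176 evaluable, or 49.6 low and 126.4 high. SE = 15 × √(4/49.6 + 4/126.4) = 5.03. For 7 versus 0, power = Φ(7/5.03 − 1.96) = 28.5%. For 9.75 versus 0, power = Φ(9.75/5.03 − 1.96) = 49%.

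| Evaluable (low / high) | Interaction SE | Power, 7 vs 0 | Power, 9.75 vs 0 | Difference for 80% power | 95% half-width, low stratum |
|---|---|---|---|---|---|
| 176 (49.6 / 126.4) | 5.03 | 29% | 49% | 14.1 | 8.3 |
| 186 (52.4 / 133.6) | 4.89 | 30% | 51% | 13.7 | 8.1 |
| 220 (62 / 158) | 4.50 | 34% | 58% | 12.6 | 7.5 |

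For 7 versus 0, noncentral-t calculations agree: 28.3%, 29.6% and 34.1%.

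**Low stratum alone.** Power for a true 7 g/m² is 38% with 176 evaluable and 45% with 220. An estimate of zero would not exclude 7, and an estimate of 7 would not exclude zero.

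**If the SD differs from 15** (assumed values, 7 versus 0, 176 evaluable): 41% at SD 12, 21% at SD 18, 18% at SD 20.

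**The population.** No calculation can settle this, because the number reporting zero output is not given. Any group with no urine output cannot be larger than the 62, so precision in it would be no better than shown for the low stratum and probably worse.

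**The case against.** The strongest reply is that the article already calls this question exploratory, twice, and claims no power for it. Low interaction power is usual for an exploratory subgroup and contradicts nothing in the sample-size section. The sentence is also hedged: it says that benefit may occur. The remark about either outcome can be read as a comment on the trial as a whole. All of that stands, and it limits the point to interpretation. It does not rescue the sentence, which turns an exploratory question into a central hypothesis under test and names a population that the described stratum does not isolate.

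A reader might go further and infer that the article would take a non-significant interaction as proof of kidney-independent benefit, and that under a true 7 versus 0 this reading would mislead about 7 times in 10 (1 − 0.29 = 0.71). The article does not support that. It gives no rule for reading a null interaction. The 71% is only how often such a result would arise in one scenario; in the 9.75 versus 0 scenario it is 42–51%.

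Nor can one say that no analysis in anuric patients is planned. The article is a condensed account, and the full protocol or the statistical analysis plan may contain one.

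**Conclusion.** The point holds as one of interpretation. The Discussion claims a test in complete anuria and draws a mechanistic implication; the contrast described is exploratory, self-reported and cut at 200 ml/24 h. An effect in the low stratum would not establish either claim.

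On size, no single power figure should be quoted. At SD 15 the range is about 29–34% or 49–58%, depending on how an absent effect in the low stratum is defined, and on dropout between 0 and 20%. No case at SD 15 reaches 80%. These figures rest on SD 15 holding in both strata, balanced allocation and equal dropout; a smaller SD would raise them and a larger one lower them. The primary endpoint, the primary analysis, the randomisation and the planned interaction test are not in question.

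**What to change.** 1. Reword the Discussion sentence to say that the trial explores effect modification by self-reported urine volume (at or below versus above 200 ml/24 h), in line with the exploratory label used elsewhere in the article. Drop the claim to test benefit in complete anuria and the implication of kidney-independent mechanisms.
2. State that a non-significant interaction is inconclusive and will not be read as benefit independent of residual kidney function. If power is quoted, give the range with its scenarios.
3. Report the treatment effect in the low stratum with its 95% confidence interval as the basis for interpretation.
4. If reported volumes were recorded as numbers, add a treatment-by-continuous-volume interaction and a descriptive estimate in patients reporting no urine. The article shows only the two-category split, so this item falls away if nothing finer was stored.

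Enrolment is complete, so the stratum cannot be enlarged; these changes carry most weight if made before unblinding. Items 1 to 3 need only wording and an estimate from the planned model, and item 4 two small analyses. The price is a weaker mechanistic claim.

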## Summary

In summary, the DAPA-HD trial (NCT05179668) is an academic, investigator-initiated, multicentre, randomized, double-blind, placebo-controlled phase 2 trial designed to evaluate the effects of dapagliflozin on cardiac structure and function in patients with kidney failure receiving maintenance haemodialysis.
